## Discussion

Physical activity is generally promoted for its well-evidenced positive impact on children’s physical and mental health [28]. However, increased participation in physical activity is also thought to lead to greater of cognitive functioning (information processing), memory, concentration, behaviour and academic achievement for children [29]. The HAPPY Study aims to examine the relationship between physical activity and behavioural well-being in primary school students, and to understand the environmental and societal factors that encourage physical activity in primary school students. This study will measure the Peaceful Playgrounds intervention; whether playground markings increases physical activity levels; if teacher training and a student leadership program encourage students to be more physically active; and whether an increase in physical activity, and social skill development will change students’ behaviour.

The HAPPY study will add to the literature around physical activity in primary schools, the effect physical activity has on behaviour, and whether interventions such as Peaceful Playgrounds successfully impact physical activity and behaviour. Within the physical activity area, the HAPPY Study will provide observational data on physical activity levels in primary school students during recess and lunch breaks. The Peaceful Playgrounds intervention will also provide teachers with resources and training to deliver physical activity sessions outside of the curriculum, so this study will also show the effectiveness of this at increasing physical activity, and encouraging student to be active. While, there is already a large number of studies around effectiveness of playground interventions [13, 14], the Peaceful Playgrounds intervention used in this study is the first we are aware of that combines environmental modifications, teacher development and student leaderships components to influence physical activity levels.

The study will also add to the body of evidence that reports on the effect play (physical activity) can have on children’s socialisation, their creativity, and their behaviour. Currently, there is limited Australian data available on this, and international studies have a focus on academic achievements, rather than the behaviour and on-task time this study will be reporting on.

A key strength of this study is the stepped wedge cluster controlled trial design. The design of the study means that time can be used as a variable to measure the effect of the intervention overtime. The design of the study also enables the research team to run the intervention in all schools over the 12-month study period. While this is thought to be ethical [30], it is also likely to decrease attrition.

If this study is successful in increasing students’ physical activity levels and modifying students’ behaviour, future research could include examining which aspects of the intervention produce which effects.

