## Methods/Design

### Study Design

The Healthy Active Peaceful Playgrounds for Youth (HAPPY) study is a 12 month, primary school-based intervention and will be evaluated using a cluster controlled trial with a stepped wedge design. Ethics approval has been obtained from an Australian University Human Ethics Committee (HREA5201500676) as well as from the New South Wales Department of Education and Communities (SERAP2015423). The HAPPY Study is registered with the Australian and New Zealand Clinical Trials Registry (ACTRN12616000575437). Principals, teachers and parents will provide written informed consent.

Following the recruitment process, data will be collected on students’ physical activity levels during lunch and recess, students’ on-task behaviour during class following lunch, and from whom the students receive social support from to be physically active. The intervention will be rolled out in a stepped wedge design. This means that all schools will start as ‘control’ schools and that the intervention will staggered across the 12-month period of the study (three steps in total) with data will being regularly collected across the period (Fig. 1). The stepped wedge design allows for an analysis of the interventions effectiveness and efficacy. As well as having the added benefit of ensuring all schools receive the intervention [16] (i.e., playground markings and teacher training). This benefit is often absent in classic Randomised Control Trials, where control groups may receive no immediate benefit from participating in research studies. This was the main rationale behind adopting this stepped wedge design.

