### Recruitment and study participation

The HAPPY Study will be conducted in six New South Wales Department of Education and Communities (NSWDEC) schools, in the Metropolitan Sydney Region (approx. 33.51°S, 151.12°E). All eligible schools will be sent an invitation to participate by the NSWDEC Schools Sport Unit. Schools that express an interest in participating will be contacted by the research team, and will be provided with more information about the study and intervention.

To participate, schools will be required to provide school level consent for the physical activity observational data collection from the principal, and all students participating in the behavioural, and the social support data collection will be required to provide parent/guardian consent. Teachers will not need to provide consent to participate in the intervention, as no information identifying them will be recorded or reported on.

All six schools will be participate in baseline data collection during the same school term and randomisation into stepped intervention groups will take place after the baseline data.

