### Physical activity during recess and lunch

Observational data will be collected on student’s physical activity levels during lunch and recess breaks, and their utilisation of playground spaces for physical activity recorded using the System for Observing Play and Recreation in Communities (SOPARC) tool (CIAFEL, Portugal: http://activelivingresearch.org/soparc-system-observing-play-and-recreation-communities). This tool will collect student’s sex, their level of physical activity and environmental factors (i.e. time of day, temperature, recess/lunch break, presence of supervision).

SOPARC is a sampling technique in which systematic and periodic scans of individuals and environmental factors within predetermined target areas are made. Each school will have two predetermined target areas, identified by the Principal of participating schools as areas that students use frequently during recess and lunch. Following SOPARC protocols developed in a previous study [20, 21], trained researchers will complete two scans of each areas at both recess and lunch, three times during each term the study is running. The researchers are blind to the conditions of the intervention. Each school in the study will therefore be scanned 12 times each term, for a total of 288 scans across all schools during the study.

A scan involves panning from left to right, and coding each student in the area by sex (male or female), intensity of activity (Sedentary, Walking or Vigorous), and whether they are a Child, Teen, Adult or Senior. Additional data recorded for each scan will include; 1. Weather variables including temperature, rain and UV levels; 2. Time of day the observations were collected, and whether this was a lunch or recess period; 3. What type of activity the students are engaged in (i.e. handball, football, dancing, clapping games) and; 4. Teacher supervision and direction of physical activity. The SOPARC tool has been used by this research team to collect physical activity and sun-safe behaviours in primary schools, and was found to be efficient to use and had high degree of reliably, with an Intraclass Corelation Coefficient (ICC) of .912 [21].

Analysis of data collected with SOPARC will be done at an individual school level, between all schools during the same collection period and then completed on all data collected during the study.

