### Statistical methods

Using the Statistical Package for Social Sciences (SPSS, v21), descriptive statistics and measures of central tendency will be used to describe the effect of the intervention from baseline to follow-up data in each step of the study.

Regression analysis will be completed for this study, to determine genuine relationships between the intervention, and the outcomes for physical activity levels, students’ on-task behaviour time, and frequency of social support for physical activity. Mixed-model ANCOVAs in SPSS will be computed, and each mixed model will be fitted to the data using the restricted maximum likelihood method. Percentage of occurrence (i.e. frequency) data will be analysed using ×2. For each mixed model, sex will be included as fixed effects, with the school included as a random effect to account for the effects of stepping by school. This is a standard statistical procedure for analysis of clustered datasets [27].

Intra-cluster comparisons will be completed between control and intervention periods, and for analyses involving school level characteristics of physical activity, the unit of analysis will be one scan of one area.

If schools decide to stop participating in the study, data pertaining to that school will not be included in the final analyses. Likewise, if a student selected for the behavioural observation component of the study decides to stop participating in the study their data will not be used in the final analyses. For all other components of the study (i.e., physical activity observation and Social Support), intention to treat principles will be followed and all possible data collected will be analysed.

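### The Discussion claims that time can be used to measure the intervention's effect over time, but the stated models name no time variable and contrast only control with intervention periods

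*Protocol article*

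**What the plan says.** The Discussion of the protocol article presents the stepped wedge as a key strength and gives this reason: "The design of the study means that time can be used as a variable to measure the effect of the intervention overtime".

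Statistical methods describes the analysis. The terms of the mixed models are given as follows: "sex will be included as fixed effects, with the school included as a random effect to account for the effects of stepping by school". The comparison is stated as "Intra-cluster comparisons will be completed between control and intervention periods". Descriptive statistics are to "describe the effect of the intervention from baseline to follow-up data in each step of the study". Neither calendar term nor time since a school crossed over is named as a model term.

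Study Design says that the roll-out is "staggered across the 12-month period of the study (three steps in total" of them). Recruitment and study participation gives six schools and a shared start: "All six schools will be participate in baseline data collection during the same school term". The section on physical activity during recess and lunch says that each school is "scanned 12 times each term, for a total of 288 scans across all schools".

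**The concern.** A school's length of exposure depends on its step: the first-step schools accumulate the most exposed terms and the last-step schools the fewest. An analysis with two states, control and intervention, pools all exposed terms into one number and cannot show how the effect develops. The article nevertheless says that the design lets the effect be measured over time.

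The pooled number is also not a neutral average. Every school contributes a first exposed term, but only the first-step schools contribute a third. The programme combines permanent markings, teacher training and student ambassadors. Its effect could fade as the markings become familiar, or grow as the training takes hold. In either case the on/off estimate would be reported as the effect of a lasting programme while leaning towards its early phase. The article gives no figure on whether the effect varies with exposure, so this is a possibility and not a prediction.

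**Working it through.** **Layout.** The stated scan counts give 288 / (12 × 6) = 4 terms. One is the shared baseline term, which leaves three for the three steps. The study figure is not shown, so I assume one step per term, two schools per step, and a start at the beginning of a term. Exposed school-terms are then 6 (first exposed term), 4 (second) and 2 (third), with 12 control school-terms. One caution: the components listed in the same section (two scans, two areas, two breaks, three times) multiply to 24 per term, not 12. The four-term reading rests on the stated 12 and 288, which agree with each other.

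**Method.** Take school-term means y with covariance V, in which any two terms of a school have correlation ρ. The on/off coefficient is the relevant row of (X'V⁻¹X)⁻¹X'V⁻¹y. Its expectation is w₁δ₁ + w₂δ₂ + w₃δ₃, where δⱼ is the true effect in exposed term j and the weights sum to 1. The article gives no ρ, so I use the range from 0 to nearly 1.

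**Model as written (no calendar term).**
- ρ = 0: the weights are the shares of exposed school-terms, 6/12, 4/12, 2/12 = 0.50/0.33/0.17.
- ρ near 1 (within-school comparison): a school with k of 4 terms exposed gives each exposed term the weight 1 − k/4, with sum of squares k(4 − k)/4. For k = 3, 2, 1 the sums are 0.75, 1.00, 0.75, and two schools each give 5.0 in total. The numerators are 2(0.25 + 0.50 + 0.75) = 3.0, 2(0.25 + 0.50) = 1.5 and 2(0.25) = 0.5. The weights are 0.60/0.30/0.10.

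**With categorical calendar term, on/off coding kept.**
- ρ = 0: subtract each term's exposed fraction (0, 1/3, 2/3, 1) from the indicator. The sum of squares is 8/3. The numerators are 2(2/3) + 2(1/3) = 2, 2(1/3) = 2/3 and 0. The weights are 0.75/0.25/0.00. The third exposed term carries no weight because every school is exposed in the last term.
- ρ near 1: removing school and term means gives 1.20/0.10/-0.30. Intermediate values are 0.80/0.23/-0.04 at ρ = 0.05 and 1.07/0.14/-0.21 at ρ = 0.5.

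**What the on/off coefficient would report (assumed effects, in points; ranges run from ρ = 0 to ρ near 1).**

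| True effect by exposed term | Simple mean | As written | With calendar term |
|---|---|---|---|
| constant 5, 5, 5 | 5 | 5 | 5 |
| fading 10, 5, 0 | 5 | 6.7 to 7.5 | 8.8 to 12.5 |
| building 0, 5, 10 | 5 | 3.3 to 2.5 | 1.3 to -2.5 |

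As written, all weights are positive. With calendar term, the building case is +0.1 at ρ = 0.15 and -0.2 at ρ = 0.2.

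**Can the design estimate effects by exposed term?** Yes. With separate effects for exposed terms 1, 2 and 3 plus calendar term, the design matrix has full rank: 7 of 7 with random school and 12 of 12 with fixed school. The cost is precision relative to the period-adjusted on/off estimate. The simple average has a standard error ratio of 0.698/0.612 = 1.14 at ρ = 0, rising to about 1.6 near 1. The third-term effect has a ratio of about 1.75 to 2.4.

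**Why calendar term is needed anyway.** In the model as written, a secular drift of 1 unit per term adds about 1.7 to 2.0 units to the on/off coefficient.

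**The case against.** The strongest reply is that the Discussion says only what the design makes possible. That is right as far as it goes: exposure-term effects are identifiable, so the design is not at fault. The gap lies between the claimed strength and the analysis stated to use it.

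A second reply is that a journal article condenses, and a full analysis plan may contain time terms. The model list is visibly incomplete, since it does not even name the intervention. This limits the force of the point, because on/off coding is inferred from the control-versus-intervention wording. It does not remove the point: the article chooses to name model terms, advertises measurement over time, and names no term that would supply it. The planned comparison of all schools within a collection period is concurrent, but does not use time since crossover either.

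Third, describing change in each step may mean by step group. Schools in one group share a crossover date, so that summary would keep exposure histories apart. I accept that reading as possible, but the summary is descriptive and has no adjustment for calendar time.

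A reader might go further and infer that the result is essentially a first-term novelty effect, or that it could reverse the sustained effect. The documents do not support this for the model as written. Later exposed terms carry 40 to 50% of the weight and no weight is negative, so effects of one sign cannot yield an estimate of the other. Both statements belong to a period-adjusted on/off model that the article does not describe.

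**Conclusion.** The point holds as a mismatch between claim and stated analysis. No stated model uses time, so the effect over time is not delivered, although the design could deliver it with limited precision. In the model as written the pooled estimate leans moderately towards early exposure. In the two illustrations it misses the exposure average of 5 by 1.7 to 2.5 points, without a change of sign. Under the natural repair for secular trend the lean becomes strong, and reversal is possible at higher correlation, so the two matters should be settled together.

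This rests on four terms, one step per term, two schools per step and an assumed range of correlation. An assumed fifth term leaves the period-adjusted pattern similar (1.00/0.33/-0.17/-0.17 at ρ = 0.5). The distortion also requires an effect that varies with exposure; a constant effect is estimated without distortion from this source under either model. It is a worthwhile, inexpensive correction and not a flaw that undermines the trial.

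**What to change.** In Statistical methods, add categorical calendar term to each mixed model and code the number of terms since crossover for each school (0, 1, 2, 3). Keep the on/off estimate. Beside it, as a supplementary analysis, report the effects by exposed term and their simple average, with intervals.

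In the Discussion, say that effects over time come from this analysis, and that the third-term effect is imprecise because it rests on the first-step schools only.

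No new data are needed, because crossover dates and collection terms are known. The cost is precision: relative to the period-adjusted on/off estimate, the standard error is about 1.14 to 1.6 times as large for the averaged effect and about 1.75 to 2.4 times for the third-term effect.

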## Abbreviations

ACTRN: Australian Clinical Trials Registry Number
ANCOVA: Analysis of covariance
BOSS: Behavioral Observation of Students in Schools
CT: Controlled Trial
HAPPY: Healthy Active Peaceful Playgrounds for Youth
HREA: Human Research Ethics Application
ICC: Intra-cluster correlation
MVPA: Moderate Vigorous Physical Activity
NSW: New South Wales
NSWDEC: New South Wales Department of Education and Communities
SERAP: State Education Research Applications Process
SOPARC: System for Observing Play and Recreation in Communities
SPSS: Statistical Package for the Social Sciences
